### Statistical analysis

2.6

Quantitative data will be presented as mean ± SD and categorical variables as frequencies within each cohort. The comparison of the statin and non-statin groups will be done using Fisher’s exact test or a χ2 test for categorical variables, and a Wilcoxon rank sum test for quantitative variables. Univariate analysis of significant predictors of an AJCC grade 0 response to NACTRT will be performed by a χ2 or Fisher’s exact test for categorical variables and logistic regression for quantitative variables. Multivariate analysis of statin use as a predictor of AJCC grade 0 responses to NACTRT will be done using multivariable logistic regression models. A Kaplan–Meier survival analysis will be used to determine the effect of statin use and AJCC TRG score on overall survival and disease-free survival. Cox proportional hazard models will be used to determine whether statin use was a significant predictor of recurrence and survival outcomes after adjusting for predicted covariates. All secondary endpoint comparisons will be made using the two-sided log-rank test with a 0.05 significance level. Assuming that OS demonstrates significance in the phase II study, the same criteria would be used for the analysis of PFS. For potential prognostic and predictive factors, multivariate analysis would be performed based on gender, metastasis occurrence from accrual to follow-up timepoint, histology subtype (diffuse, intestinal), and measurable disease (yes, no).

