#### Screening

2.3.1

All patients diagnosed as having rectal cancer will undergo a standard staging workup that includes but may not be limited to a colonoscopy, biopsy, pelvis MRI, and contrast-enhanced computed tomography (CECT) of the thorax and abdomen, carcino embryonic antigen (CEA), complete blood count and biochemistry tests [random blood sugar (RBS), liver function test (LFT), and renal function test (RFT)]. This is part of the standard care. Treatment decisions are taken by a multi-disciplinary tumor board (MDTB). Previously untreated rectal cancer patients who are planned for NACTRT will be screened for the study and an anonymized screening log will be maintained.

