#### Randomization

2.3.3

Patients will be randomized in a 1:1 ratio using block randomization to rosuvastatin and NACTRT or NACTRT alone. An independent statistician will generate the randomization code and independent research staff will inform the study team of the allocation. A randomization log will be maintained by the study team.

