### Sample size and duration of the study

2.4

Each year, approximately 180–200 rectal cancer patients receive NACTRT at our hospital, with approximately 70% undergoing surgery and 15%–20% developing progressive disease. The current pCR rate at our hospital following NACTRT is approximately 15%, while the literature indicates a pCR rate of 25%–30% with statin therapy. We hypothesize that rosuvastatin can increase the pCR rate by 10%, from 15% to 25%. To detect a 10% difference in pCR rates, with a two-sided alpha of 0.10 and 80% power, a sample size of 288 patients would be required. Factoring in a 10% attrition rate, the total sample size increases to 316. Approximately 500–600 patients will need to be screened to enroll 316 participants. It is estimated that accrual and analysis will take approximately 3 years to complete.

A follow-on phase III trial is also will be planned depending on the success of the phase II study, which will compare the 3-year DFS in the two arms. All the patients in the phase II study will be included in the survival statistics in the follow-on phase III study which will be statistically powered for survival. Assuming that the addition of rosuvastatin to NACTRT will improve the 3-year DFS from 60% to 67%, our calculated sample size will be 1,135 subjects (567 in the control group and 568 in the treatment group) (a two-sided log-rank test with 80.0% power at a 0.050 significance level). This assumes a uniform accrual pattern across time periods and 10% dropout rate. If we move on to the phase III study, another 4 years will be required for accrual. The total duration will be 7 years for accrual and 3 years for follow up.

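### The primary pCR comparison is left as an unadjusted Fisher's exact or χ2 test beside an unranked logistic model; naming one analysis, adjusted for baseline stage and CEA, would be better defined and modestly more efficient.

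*Protocol article*

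**What the plan says.** Section 2.6 (Statistical analysis) has one general rule for comparing the arms on categorical variables: "The comparison of the statin and non-statin groups will be done using Fisher’s exact test or a χ2 test for categorical variables". Section 2.5 makes pCR the primary efficacy variable, and no separate test is named for it, so the general rule applies.

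The same section then lists two further analyses of AJCC grade 0, which section 2.3.6 equates with pCR:
- "Univariate analysis of significant predictors of an AJCC grade 0 response to NACTRT", by χ2 or Fisher for categorical factors and logistic regression for quantitative ones;
- "Multivariate analysis of statin use as a predictor of AJCC grade 0 responses to NACTRT will be done using multivariable logistic regression models".

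No covariates are given for that model, and it is not ranked against the unadjusted test. The only factors listed are for the separate analysis of prognostic and predictive factors: gender, later metastasis, histology subtype and measurable disease. Baseline stage and CEA are not among them, and later metastasis arises after randomisation.

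The baseline data exist. The standard workup in section 2.3.1 includes "pelvis MRI, and contrast-enhanced computed tomography (CECT) of the thorax and abdomen, carcino embryonic antigen (CEA", and eligibility in Table 2 spans clinical and radiological T2 to T4 with any N. On allocation, section 2.3.3 says "Patients will be randomized in a 1:1 ratio using block randomization to rosuvastatin and NACTRT or NACTRT alone" and names no stratification factor. The sizing statement in section 2.4 is "with a two-sided alpha of 0.10 and 80% power, a sample size of 288 patients would be required".

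**The concern.** Followed as written, the effect of rosuvastatin on pCR can be tested three ways: χ2, Fisher and multivariable logistic regression. Nothing says which one decides whether phase II is positive, and the move to phase III depends on that result. The χ2 and Fisher tests differ noticeably in power at this sample size, and the logistic result can differ from both.

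Stage and CEA are measured before randomisation but play no part in the primary comparison. If they predict pCR, using them would make better use of data already in hand and would account for chance differences in stage between the arms. At stake are a few points of power and a decision rule that is not fixed before the data are seen.

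**Working it through.** **Inputs.** From section 2.4: pCR 15% versus 25%, alpha 0.10 stated as two-sided, power 80%, 288 evaluable patients. With the 1:1 ratio of section 2.3.3 this is 144 per arm. Assumed: how strongly baseline stage and CEA predict pCR, because the protocol gives no figure. They are represented by one normally distributed baseline score with AUC from 0.50 (no information) to about 0.74.

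**Step 1: the plan's own figure.** For an unadjusted comparison of two proportions,

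n per arm = [z_α √(2·p̄(1−p̄)) + z_β √(p₁(1−p₁) + p₂(1−p₂))]² / (p₂−p₁)²,

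with p̄ = 0.20, so that √(2·0.20·0.80) = 0.5657 and √(0.1275 + 0.1875) = 0.5612.
- Two-sided 0.10: (1.645·0.5657 + 0.842·0.5612)² / 0.01 ≈ 196.8, so 197 per arm, 394 in total.
- One-sided 0.10: (1.282·0.5657 + 0.842·0.5612)² / 0.01 ≈ 143.4, so 144 per arm, 288 in total.

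The stated 288 is therefore an unadjusted two-proportion calculation at one-sided 0.10. At the stated two-sided 0.10 it gives 68% power by formula. That mismatch is a separate matter. Here it explains why the power figures below start near 69% and not 80%.

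**Step 2: χ2 against Fisher.** Exact enumeration of all binomial outcomes, 144 per arm:

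| Two-sided level | Test | Power, 15% vs 25% | Size at 15% |
|---|---|---|---|
| 0.10 | χ2 | 69.1% | 10.0% |
| 0.10 | Fisher | 63.3% | 7.2% |
| 0.20 (matches one-sided 0.10) | χ2 | 80.7% | 20.4% |
| 0.20 | Fisher | 76.1% | 14.7% |

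Fisher costs 69.1 − 63.3 = 5.8 points at 0.10 and 80.7 − 76.1 = 4.6 points at 0.20.

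**Step 3: can the verdicts differ?** Take 22/144 against 34/144 (15.3% vs 23.6%). The pooled rate is 56/288 = 0.1944, so z = (12/144) / √(0.1944·0.8056·2/144) = 1.787 and the χ2 p-value is 0.074. Fisher gives 0.101. At 0.10 one test is positive and the other is not. Across all outcomes the two disagree in 5.8% of trials at 15% vs 25% and in 2.8% of trials when both rates are 15%.

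**Step 4: does choosing between χ2 and Fisher inflate type I error?** Every Fisher rejection at 0.10 is also a χ2 rejection, with no exceptions. Taking the more favourable of the two therefore has the size of χ2 alone: 9.97% at a common rate of 15% and 10.17% at 20%.

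**Step 5: adding the logistic model to the choice.** In simulation (10,000 trials per setting, AUC about 0.64 to 0.74), the three tests do not all agree in roughly 9% to 16% of trials under the alternative. Taking whichever is significant brings type I error to about 11% to 13%.

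**Step 6: gain from adjustment.** Simulated power at two-sided 0.10, 144 per arm, marginal rates held at 15% and 25%:

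| Assumed AUC | Unadjusted χ2 | Adjusted logistic | Difference (points) |
|---|---|---|---|
| 0.50 | 69.6% | 68.8% | −0.8 |
| 0.59 | 68.7% | 68.6% | −0.1 |
| 0.64 | 69.1% | 70.1% | +1.0 |
| 0.71 | 68.9% | 71.3% | +2.4 |
| 0.74 | 69.6% | 74.2% | +4.6 |

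Type I error of the pre-specified adjusted model stays near 10%.

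**The case against.** The strongest reply is that nothing here is wrong. An unadjusted comparison of two proportions is valid under 1:1 randomisation, and its error rate already allows for chance imbalance in stage. It is also the kind of test that 288 was calculated for. The adjustment gain depends on a prognostic strength that the protocol does not give, and it vanishes if stage and CEA predict weakly. An adjusted model of the same endpoint is already planned, and its covariate list and the ranking of analyses may sit in a fuller plan that is not shown. The Fisher-or-χ2 wording is general language for all categorical variables. All of this stands, and it is why the point is an improvement and not a correction.

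Some stronger readings are tempting but not supported:
- *Free power.* A reader might infer that adjustment is costless and certain to help. At AUC 0.50 to 0.59 there is no gain.
- *Covariates selected by univariate significance.* The wording "Univariate analysis of significant predictors of an AJCC grade 0 response to NACTRT" followed by a multivariable model suggests this, but section 2.6 does not say that the first analysis selects covariates for the second.
- *Inflated false positives from the Fisher-or-χ2 choice.* Step 4 rules this out. A modest inflation appears only if the logistic model is also treated as an alternative route to a positive result.
- *No stratification at all.* The article names no factor; a condensed article's silence does not show that there is none.

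What the reply does not remove is that the article does state an analysis for the primary endpoint, and states it as an open choice beside a second model of the same endpoint.

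**Conclusion.** The point holds as a recommendation on pre-specification and efficiency. The primary pCR comparison is valid as written but not fixed to one test, and it leaves baseline stage and CEA unused.

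The firmer part is the choice of test. Fisher instead of χ2 costs about 6 points of power at two-sided 0.10 and about 5 at one-sided 0.10, and the two can disagree on the same data. These figures rest only on the protocol's rates and 144 per arm. The softer part is adjustment: roughly 0 to 5 points, resting entirely on an assumed AUC of 0.50 to 0.75 for the combined baseline information. Neither part shows bias, and the Fisher-or-χ2 choice alone does not raise type I error.

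**What to change.** Name one primary analysis of pCR in section 2.6: logistic regression of pCR on arm with clinical T stage, clinical N stage and log CEA as covariates, fixed in advance and not chosen by univariate significance. Report the standardised (marginal) risk difference with a confidence interval at the primary alpha. Keep the unadjusted χ2 test as a sensitivity analysis. Do not use Fisher's test for the primary comparison: expected pCR counts are about 144 × 0.15 = 22 and 144 × 0.25 = 36, so small counts give no reason for it. State that any other model of pCR is supportive.

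The change needs no new data or visits. It should be made before the data are analysed by arm, which matters more because the trial is open-label and already running. The costs are a slightly more complex primary model and a simple rule for missing CEA, set at the same time.

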**Methods:**

This is a prospective, randomized, open-label phase II/III study. The phase II study has a sample size of 316 patients (158 in each arm) to be accrued over 3 years to have 288 evaluable patients. The standard arm will receive NACTRT while the intervention group will receive 20 mg rosuvastatin orally once daily along with NACTRT for 6 weeks followed by rosuvastatin alone for 6–10 weeks until surgery. All patients will be reviewed after repeat imaging by a multidisciplinary tumor board at 12–16 weeks after starting NACTRT and operable patients will be planned for surgery. The pathological response rate, tumor regression grade (TRG), and post-surgical complications will be recorded.

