#### Assessment of response

2.3.6

Clinical and radiological assessment will be done at 6–8 weeks after completion of NACTRT. Eligible patients will undergo standard surgery (anterior resection, abdominoperineal resection, inter-sphincteric resection, or multi-visceral resection) according to the level and extent of growth. If the reassessment MRI at 12–14 weeks after completion of NACTRT shows inoperable disease, then the patient will be deemed a non-responder and analyzed as part of the non-pCR group. These patients, if on the rosuvastatin arm, will stop the statin on the day they are deemed inoperable by the MDTB. These patients will receive further chemotherapy to downstage the disease as per the current standard of care. A histopathological examination will be conducted for the patients operated on and the pathological response rate and tumor regression grade (TRG) will be judged according to the American Joint Committee on Cancer (AJCC) (**Appendix 1** in **Supplementary Material**). A pCR is defined as no residual cancer found on histological examination of the TME specimen (Grade 0 AJCC or Grade 1 Mandard’s). The pathologist assessing the specimen will be blinded to the treatment that the patient received.

Following surgery and the availability of the histopathology report, the patient would have completed the active phase of the study and will be followed up according to standard follow-up protocol. Survival details will be collected at each follow-up visit or telephonically if the patient misses a visit for any reason.

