#### End of study visit

2.3.7

Patients will receive rosuvastatin for 12–16 weeks, with the treatment being discontinued 1 day prior to surgery for operable patients. The final study visit for these patients will coincide with their MDTB appointment, where the final surgical histopathology report (approximately 10–14 days post-surgery) will be reviewed. For patients deemed inoperable, the study will conclude on the day the decision of inoperability is made. At this visit, a final safety follow-up and pill count will be conducted. Following this, there will be no further active intervention, and patients will be monitored for survival. No protocol-mandated imaging or re-evaluation is planned; patients will be followed according to standard surveillance guidelines for rectal cancer patients who have undergone multimodality treatment.

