### Statistical consideration

2.5

A) The primary efficacy variable is a pathological complete response which is defined as the absence of microscopic tumors in the resected specimens in patients who undergo surgery following neoadjuvant chemoradiotherapy.

B) The secondary efficacy variables are toxicity and 3-year DFS.

C) Toxicity will be assessed as detailed below. The NCI Common Terminology Criteria for Adverse Events version 4 (NCI CTCAE v4.03) will be used to classify and grade the intensity of adverse events during and after chemo-radiotherapy. The worst grade of each toxicity episode will be recorded. All events regardless of attribution will be graded so as to ensure objectivity in reporting as per accepted international guidelines. The details will be entered in the dataset.

D) Any adverse event that occurs from the day of randomization until the end of study visit will be defined as an acute adverse event. Events that occur thereafter will be defined as chronic adverse events. Both acute and chronic adverse events will be recorded however only events happening till 30 days after surgery will be reported and not beyond.

E) Postoperative morbidity and mortality will be any event occurring from the day of surgery until 30 days.

F) Disease-free survival is defined as the time from the date of randomization until the date of disease recurrence or until death from any cause.

G) Progression-free survival (PFS) is defined as the time from the date of randomization until the date of disease recurrence or until death from any cause. If there is a clinical suspicion of progression, further workup and management will be as per the institutional standard. Progression will be assessed by the investigator using appropriate workup and investigations, as per routine care.

H) Overall survival is defined as the time from the date of randomization until the date of death from any cause.

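### Survival curves by tumor regression grade run from randomization although the grade exists only after surgery, and section 2.6 does not say whether inoperable patients enter them (minor)

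*Protocol article*

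**What the plan says.** Section 2.6 (Statistical analysis) names one survival method for two quite different groupings: "A Kaplan–Meier survival analysis will be used to determine the effect of statin use and AJCC TRG score on overall survival and disease-free survival". One grouping is the randomized arm. The other is a pathology result.

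Section 2.5 gives each endpoint one time origin. Item F: "Disease-free survival is defined as the time from the date of randomization until the date of disease recurrence or until death from any cause". Item H: "Overall survival is defined as the time from the date of randomization until the date of death from any cause".

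Section 2.3.6 (Assessment of response) shows who receives a grade: "A histopathological examination will be conducted for the patients operated on and the pathological response rate and tumor regression grade (TRG) will be judged". On timing, the abstract's Methods places the tumor-board review "at 12–16 weeks after starting NACTRT and operable patients will be planned for surgery", and section 2.3.4.2 gives 12–16 weeks of statin therapy up to surgery. Section 2.3.7 adds a further delay before the grade is known; it describes a visit "where the final surgical histopathology report (approximately 10–14 days post-surgery) will be reviewed".

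For a patient whose reassessment MRI shows inoperable disease, section 2.3.6 says: "then the patient will be deemed a non-responder and analyzed as part of the non-pCR group". Section 2.3.9 treats a different group separately: patients who respond but are not operated on are left out of the phase II analysis. Section 2.6 does not say whether inoperable patients appear in the TRG curves.

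**The concern.** Randomization is the right origin for statin versus control, because the arm is known at that moment. TRG is not known then. A patient has to live and remain operable for about three to four months before a grade can exist. Sorting patients at time zero by something learned later has two possible consequences, depending on who enters the curves.

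- **Graded patients only.** No graded patient can die before surgery, and few can have a DFS event. All curves are lifted.
- **Inoperable patients added to the non-pCR group.** Early failures are then all placed on one side, and pCR appears to carry a survival advantage even if it has none.

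The second case matters more, because section 1.1 argues from the better survival of patients with pCR, citing 5-year DFS of 83% versus 66%. A gap that comes from how the groups are formed could be read as confirming that argument.

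**Working it through.** **Plan's own figure.** No figure is stated for the TRG analysis. The only stated figure built on the DFS rates used here is the phase III size of 1,135 (section 2.4: 60% vs 67% at 3 years, two-sided 0.05, 80% power, 10% dropout).
- Hazard ratio = ln(0.67)/ln(0.60) = 0.784, which needs 531 events (Schoenfeld) or 536 (Freedman).
- With exponential survival, 4 years of uniform accrual and 3 years of follow-up, the mean event probability is 0.523. That gives 1,016 or 1,026 patients, and after dividing by 0.90, 1,129 or 1,140.
- This agrees with 1,135, so a constant hazard through 60% at 3 years is a fair working model. With 7 years of accrual the result is 973–982, which does not agree.

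**Case 1: graded patients only.**
- Yearly hazard h = −ln(0.60)/3 = 0.1703.
- Share with an event by time t: 1 − exp(−ht). Week 12 (t = 12/52.18 = 0.230 years): 3.8%. Week 16 (t = 0.307): 5.1%.
- 3-year DFS on the randomization clock, given event-free at surgery: 0.60/0.9616 = 62.4% and 0.60/0.9491 = 63.2%.
- Overstatement: 2.4 to 3.2 points. At the statin-arm assumption of 67%, the same steps give 69.1% and 69.8%, or 2.1 to 2.8 points.
- Effect on the comparison between grades, by simulation with no true TRG effect (316 patients, 3,000 runs, two-sided 0.05; 20% with TRG 0 is an assumption): the log-rank test rejects in 4.7–5.4% of runs from randomization and 4.6–5.4% from surgery. With surgery at 16 weeks for TRG 0 and 12 weeks for the others, it rejects in 4.1%, with a gap of 0.6 points.

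**Case 2: inoperable patients pooled as non-pCR, no true TRG effect.**
- Inputs: 70% operated, pCR 15%, progressive disease 15–20% (section 2.4); overall 3-year DFS 60%. Assumed: the 15% applies to all patients; 3-year DFS n in unoperated patients is 20% or 30%; the pooled share w is the 15–20% with progression.
- DFS s in operated patients: 0.60 = 0.70s + 0.30n, so s = 0.771 (n = 0.20) or 0.729 (n = 0.30).
- Operated non-pCR share: 0.70 − 0.15 = 0.55. Non-pCR group DFS = (0.55s + wn)/(0.55 + w).

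| w | n | s (also pCR group) | Non-pCR group | False gap |
|---|---|---|---|---|
| 0.15 | 0.20 | 0.771 | 0.649 | 12.2 points |
| 0.15 | 0.30 | 0.729 | 0.637 | 9.2 points |
| 0.20 | 0.20 | 0.771 | 0.619 | 15.2 points |
| 0.20 | 0.30 | 0.729 | 0.614 | 11.4 points |

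The simulation agrees in direction and order of size. If 5%, 10%, 15% or 20% of patients fail before surgery and are added to the non-TRG-0 group, the test rejects in 6.8%, 17.6%, 33.6% or 54.8% of runs. The false 3-year gaps are about 4, 8, 11 and 15 points. The protocol does not say when the 15–20% progress, so these are a range.

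**The case against.** The strongest reply is that every graded patient must reach surgery, so the event-free stretch is common to all grades and does not favor any one of them. This stands: the simulated error rates are at their nominal level, and what remains in case 1 is a modest lift in absolute survival.

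Next, a curve by TRG score can contain only patients with a score, and the non-pCR rule in section 2.3.6 concerns response classification. This is the more natural reading, but the rule speaks of how the patient is analyzed and section 2.6 sets no limit on it. Case 2 is therefore open, not planned.

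Third, a landmark or analysis set for a secondary, non-randomized curve is commonly left to an SAP, which is not shown. That lowers the weight of the point. It does not remove it, because the clock and the grouping are both stated in this document and do not fit each other.

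A reader might infer three stronger claims, which the documents do not support:
- **The prognostic-factor objective is answered by these curves.** Section 2.6 gives that objective its own multivariate analysis, on gender, metastasis during follow-up, histology and measurable disease. TRG is not listed.
- **The false gap is 15–20 points.** This pools all 30% unoperated patients: (0.55s + 0.30n)/0.85 = 0.570 or 0.577, so gaps of 20.2 or 15.1 points. Section 2.3.6 pools only inoperable patients, and section 2.3.9 takes unoperated responders out of the phase II analysis.
- **The phase III decision rests on these curves.** Section 2.1 ties it to feasibility, safety and efficacy in the statin arm.

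**Conclusion.** The point holds as a minor one. The stated time origin does not suit a factor determined after surgery.

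With graded patients only, the harm is an overstatement of 3-year DFS by about 2.4–3.2 points, assuming a constant hazard and surgery at 12–16 weeks. The comparison between grades is nearly unbiased, so it would be wrong to say that immortal time creates a difference between grades.

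With inoperable patients pooled as non-pCR, a false gap of roughly 9–15 points is possible. It rests on 15–20% being pooled and on an assumed 20–30% 3-year DFS in unoperated patients, for which the protocol gives no figure. That pooling is neither stated nor excluded.

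The randomized statin comparison, the listed prognostic-factor analysis and the phase III decision are not affected.

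**What to change.** Amend section 2.6 as follows:
- Keep randomization as time zero for statin versus control.
- For TRG or pCR as a factor, start the curves at surgery, or at a fixed landmark, and include only operated patients who are event-free at that point.
- Show inoperable patients as a separate group in these analyses, not as non-pCR.

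The cost is a sentence or two of text. The date of surgery is needed in any case, because section 2.5 counts postoperative events from that day. The downside is that the TRG analysis then applies only to operated patients, who are the only ones with a grade.
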